## Abstract

Pre-eclampsia is a leading cause of maternal and perinatal morbidity and mortality. The burden of disease lies mainly in low-middle income countries. The aim of this project is to establish a pre-eclampsia biobank in South Africa to facilitate research in the field of pre-eclampsia with a focus on phenotyping severe disease.The approach of our biobank is to collect biological specimens, detailed clinical data, tests, and biophysical examinations, including magnetic resonance imaging (MRI) of the brain, MRI of the heart, transcranial Doppler, echocardiography, and cognitive function tests.Women diagnosed with pre-eclampsia and normotensive controls are enrolled in the biobank at admission to Tygerberg University Hospital (Cape Town, South Africa). Biological samples and clinical data are collected at inclusion/delivery and during the hospital stay. Special investigations as per above are performed in a subset of women. After two months, women are followed up by telephonic interviews. This project aims to establish a biobank and database for severe organ complications of pre-eclampsia in a low-middle income country where the incidence of pre-eclampsia with organ complications is high. The study integrates different methods to investigate pre-eclampsia, focusing on improved understanding of pathophysiology, prediction of organ complications, and potentially future drug evaluation and discovery.

## 1. Introduction

Pre-eclampsia is one of the most serious complications of pregnancy and affects 3–8% of pregnancies worldwide [1]. It is a leading cause of maternal and perinatal morbidity and mortality [2]. Globally, pre-eclampsia is responsible for more than 60,000 maternal deaths annually, and in South Africa, hypertensive disorders of pregnancy account for 14% of all maternal deaths [3].

The pathogenesis of pre-eclampsia is not yet fully elucidated. It likely involves maternal, foetal, and placental factors, resulting in relative placental under-perfusion, hypoxia, and ischaemia [1]. The placenta then releases anti-angiogenic factors causing endothelial dysfunction resulting in a multi-system disorder [4]. Hypertension is the hallmark feature and other systems including renal, cardiovascular, respiratory, haematological, hepatic, cerebrovascular, and the fetoplacental unit can be involved [5]. In its most severe form, it can cause seizures (eclampsia), cerebrovascular events, pulmonary oedema, cardiac failure, acute kidney injury, haemolysis, elevated liver enzymes, low platelet (HELLP) syndrome, disseminated intravascular coagulation, sub-capsular liver haematoma or rupture, and even death [6,7,8,9,10].

Pre-eclampsia is a disease that is only observed in humans. No animal models of pre-eclampsia have the ability to exactly mimic the true pre-eclampsia state due to differences in placentation among mammals [11]. It is imperative that critical laboratory observations are made on human tissues.

Biobanks enable research for which clinical information and analyses from biological samples are efficiently used and combined in more than one project. Biobanks can also be used in collaboration with international biobanks to achieve sufficient power and generalisability in rare outcomes.

Low-and-middle-income countries (LMIC) have a higher incidence of pre-eclampsia, more complications, and bear the major burden of global maternal and perinatal deaths [6]. For these reasons, it makes sense to establish a biobank in an area with a high incidence of pre-eclampsia. Researchers from Tygerberg Hospital, Stellenbosch University, have been investigating pre-eclampsia for many years [12,13,14,15,16]. Tygerberg hospital is a referral center servicing a population of over 2 million people. The Obstetrics Department only manages complicated pregnancies (such as those affected by severe, or preterm pre-eclampsia) and delivers approximately 8000 women per year. The high-risk referral service is supported by maternal-foetal medicine sub-specialists, critical care specialists, and neonatologists. The occurrence of pre-eclampsia and its complications is high in South Africa which is expected for a low-and-middle-income country. Unfortunately, the exact incidence is not known. The academic centre at Tygerberg Hospital is, therefore, an ideal service to embed a pre-eclampsia biobank.

The research team at Tygerberg Hospital also has established collaborations with leading academic centres in Australia, Sweden, The Netherlands, the United Kingdom, and the United States of America. Such collaborations enable linkage of a unit that has an extremely high incidence of pre-eclampsia, and in particular, pre-eclampsia with severe features, with other research leaders in the field of pre-eclampsia. These collaborations can enable us to make important discoveries about why different organs are affected in pre-eclampsia, findings that may improve the clinical care of women.

## 2. Aims and Objectives

To establish a pre-eclampsia database and biobank at Tygerberg Hospital, Stellenbosch University and to facilitate research in pre-eclampsia, detailed data are collected according to an international consensus of core predictors and outcomes in pre-eclampsia research [17]. The aims of this approach are to enable the discovery of possible predictors and diagnostic tools for organ complications in pre-eclampsia and to develop the understanding of the underlying pathophysiology further with a focus on different organ complications. We collect biological specimens including plasma, saliva, cerebrospinal fluid, urine, placenta, and umbilical cord blood (mixed venous–arterial). In subgroups, we perform specialised examinations to assess organ dysfunction, reveal underlying pathophysiological pathways, and aim to relate the findings to predictors and biomarkers. These examinations include cerebral magnetic resonance imaging (MRI), cardiac MRI, transcranial Doppler, echocardiography, and cognitive function testing.

## 3. Materials and Methods

The study is registered at the International Standard Randomised Controlled Trial Number (ISCRTN) with trial registration number ISRCTN10623443.

### 3.1. Study Design and Population

We include women who are admitted to Tygerberg Hospital for the birth of their baby. Cases (women with pre-eclampsia) are included before or after delivery depending on presentation. Controls (women with normotensive pregnancies) are recruited when admitted for delivery or at a visit to the outpatient clinic. For the controls, samples are collected at inclusion and delivery. Cases are seen daily and clinical information and samples are collected serially until discharge. All participants are contacted telephonically in the postpartum period. Data are collected prospectively and from the medical charts on maternal health and neonatal outcomes (Figure 1).

#### Inclusion and Exclusion Criteria

All women with pre-eclampsia who are admitted to Tygerberg hospital are eligible for inclusion. Our controls are women who deliver at Tygerberg without the hypertensive disease. Pre-eclampsia is defined according to the International Society for the Study of Hypertension in Pregnancy (ISSHP) [18]. Both women with pre-eclampsia without severe features and pre-eclampsia with end-organ complications are eligible for inclusion. End-organ complications are defined according to the ISSHP classification system and include haemolysis, elevated liver enzymes, and low platelets (HELLP) syndrome, eclampsia, pulmonary oedema, renal impairment, and acute severe hypertension [18]. All parameters are included in the online database described below, and women can thus be classified according to different classification systems. All participants must be competent to provide informed consent before enrolment. If they are minors, they need to read and sign the assent form, and a parent or guardian must sign consent. All individual studies originating from the biobank require a unique ethical approval.

### 3.2. Collection of Clinical Information

Clinical information is collected on datasheets and entered into an online secure password-protected Research Electronic Data Capture (REDCap) database. The data collection includes information on the participant’s age, gravidity, parity, medical history, current pregnancy information, and outcome of the pregnancy. Only the principal investigators have access to patient identifying information and each participant is allocated a study number. The variables collected in the database correspond to the recommended core demographics, predictors, and outcomes listed in “*Strategy for standardization for pre-eclampsia research design*” by the international group Co-Lab for harmonisation of pre-eclampsia research (Table 1) [17]. The women are also interviewed at inclusion with a short questionnaire regarding signs and symptoms specific for pre-eclampsia (Table 1).

### 3.3. Sample Collection and Storage

Samples are collected by research midwives. After a blood sample is drawn, it is centrifuged, aliquoted, and frozen within two hours of collection. The same procedure is performed for cerebrospinal fluid and umbilical cord blood. Saliva and urine are frozen directly and are not centrifuged. Placental samples are taken at four sites on the maternal and foetal surfaces of the placenta. They are stored in RNAlater for at least 48 h and then frozen. All samples are stored in a minus 70 °C freezer which has an electronic temperature monitoring system. All samples are labelled only with the study number, sample number, and date. Samples collected for the biobank are presented in Table 2.

### 3.4. Questionnaires and Biophysical Examinations

#### 3.4.1. Cognitive Function Testing

Cognitive function is assessed subjectively and objectively as close to discharge as possible. The subjective function is assessed using the Cognitive Failure Questionnaire (Supplemental Figure S1). Cognitive function is also assessed objectively using the Montreal Cognitive Assessment (MoCA) (Supplemental Figure S2). A detailed description of the cognitive function tests can be found in the Supplementary Methods Section.

#### 3.4.2. Brain MRI

For women with eclampsia and women with pre-eclampsia with severe features without eclampsia as a control group, we perform MRI examinations on entry into the study. We use a 1.5 Tesla scanner, used in clinical practice, at the Department of Radiology at Tygerberg University Hospital. The MRI protocol includes sequences for evaluation of brain morphology including infarcts, oedema, and haemorrhages, as well as assessment of arterial spasm and cerebral perfusion. Imaging sequence information can be found in the Supplementary Methods Section.

#### 3.4.3. Transcranial Doppler

Transcranial Doppler examination is performed in a subgroup of women to evaluate the cerebral perfusion pressure and dynamic cerebral autoregulation on entry into the study and for some women also before discharge from the hospital and in addition before and after vasoactive medication. Both women with normotensive pregnancies, pre-eclampsia without severe features, and pre-eclampsia with severe features are eligible for transcranial Doppler examination. This is performed by locating the middle cerebral artery bilaterally by the Doppler technique and simultaneously recording continuous blood pressure and end-tidal CO_2_. A detailed description of the methodology can be found in the Supplementary Methods Section.

#### 3.4.4. Echocardiography and Cardiac MRI

A subgroup of cases (women with pulmonary oedema) and controls (women with pre-eclampsia without pulmonary oedema and women with normotensive pregnancies) have echocardiograms and cardiac MRI on entry into the study. Investigations are performed by two cardiologists according to a predefined protocol that can be found in the Supplementary Methods Section.

### 3.5. Statistics

Results from echocardiography, MRI, and cerebral Doppler will be calculated by two independent interpreters blinded to groups and entered manually into the database. MR data will be analysed in collaboration with Uppsala University by neuroradiologists, blinded to groups. Blood samples will be analysed for placental, cardiac-, renal-, neurological- and endothelial biomarkers, using standardised platforms when available and for the remaining analyses through manual enzyme-linked immunosorbent assay (ELISA) analyses in duplicates. Inter- and intra-assay coefficients of variation will be aimed at below 10%.

Demographics will be presented as medians or means as appropriate by distribution. Comparison between groups will be analysed by Student’s *t*-test or Mann–Whitney u-test with means or medians and confidence intervals or interquartile range, as appropriate according to the distribution of the variables. When comparing multiple groups, the Kruskal–Wallis test or one-way ANOVA will be used as appropriate according to the distribution of the variables. Correlations will be analysed by Pearson’s r or Spearman’s rho, as appropriate by the distribution of the variable. Regression analyses, unadjusted and adjusted, will be performed to adjust for known confounding variables. A total of 10 cases per variable at the lowest will be considered appropriate to avoid overfitting of the model. All statistical analyses will be performed in SPSS or R.

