#### Power Calculations

Tygerberg University hospital has approximately 8000 high-risk deliveries yearly. Pre-eclampsia affects a large proportion of these deliveries but the exact numbers are not known.

Prospective power calculations for some investigations will not be possible since no reference values or results exist. In addition, the biobank is designed to be open for future research on pre-eclampsia where the research question to date might not be known. Some examples of power calculations for planned analyses are given below.

Cerebral blood flow regulation: To detect a difference in dynamic cerebral autoregulation index of 1, 2 with a standard deviation (SD) of 1.5, 25 women are required in each group [19]. Cerebral biomarkers: To detect a difference of 4 pg/mL between cases and controls for NfL with an SD of 5, 25 women are required per group [20].

In order to extend the comparisons to correlations and sub-analyses, the initial sample size for PROVE was set to 100 women with eclampsia, 50 women with pulmonary oedema, and 50 women in each control group before the first round of analyses are initiated.

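### Section 3.5 names equal-variance tests while eclampsia is planned at 100 against 50 in each other group; naming the Welch versions would be a cheap, minor improvement

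*Protocol article*

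**What the plan says.** For two groups, section 3.5 states: "Comparison between groups will be analysed by Student’s *t*-test or Mann–Whitney u-test". For several groups, "the Kruskal–Wallis test or one-way ANOVA will be used as appropriate according to the distribution of the variables". In both cases the only criterion is the distribution of the variable. Unequal spread is not mentioned, and no unequal-variance version is named.

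The Power Calculations section sets the initial sample at "100 women with eclampsia, 50 women with pulmonary oedema, and 50 women in each control group". Eclampsia is therefore twice the size of any group it is compared with, while pulmonary oedema and the control groups are equal to each other.

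The same section gives two worked examples, both with equal groups and one common SD: the autoregulation index, "with a standard deviation (SD) of 1.5, 25 women are required in each group", and the biomarker example, "To detect a difference of 4 pg/mL between cases and controls for NfL with an SD of 5, 25 women are required per group". Significance level, sidedness and power are not stated.

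**The concern.** Student's t-test and the classical ANOVA F test pool the group variances. With equal group sizes they tolerate unequal SDs well; with unequal sizes they do not. If the larger group is the more variable one, the pooled standard error is too large, and the test is conservative and loses power. If the smaller group is the more variable one, the pooled standard error is too small and false positives exceed the nominal level. Confidence intervals for mean differences carry the same error.

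The planned 2:1 ratio for eclampsia, and the less even sizes enrolled so far (86, 43, 23, 54 and 38 in Table 3), are the setting in which this can matter. Choosing by distribution does not deal with it: a roughly normal variable with different SDs would still go to the pooled test.

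**Working it through.** **1. The plan's own figure.** Inputs: a difference of 1.2 (printed as 1, 2) with SD 1.5, and a difference of 4 with SD 5. Both are a standardised effect of 0.8. Assuming two-sided 5% and 80% power, n per group = 2(1.96 + 0.842)²/0.8² = 24.5, so 25. The stated 25 is reproduced. At 25 v 25, Student's power stays at about 79% for SD ratios from 0.5 to 2, so these examples are not disturbed.

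**2. Method for unequal sizes.** The pooled test uses, on average,

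V_pooled = [((n1−1)σ1² + (n2−1)σ2²)/(n1+n2−2)] × (1/n1 + 1/n2),

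whereas the true variance of the mean difference is V_true = σ1²/n1 + σ2²/n2. When V_pooled/V_true is below 1 the test is liberal; above 1 it is conservative. Exact error rates come from simulation under normality at an assumed two-sided 5% (400,000 runs for two groups, 200,000 for ANOVA).

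**3. Planned sizes, Table 3 SDs.** The neurology column stands in for eclampsia (82 of its 86 women had it), against pulmonary oedema, pre-eclampsia without organ complications, and normotensive women. The variables are age, BMI, gestation at first antenatal visit, gestation at delivery and birthweight.

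- Most liberal: gestation at delivery, SD 4.3 (n = 100) v 5.0 (n = 50). Pooled variance = (99×18.49 + 49×25)/148 = 20.65; V_pooled = 20.65×0.03 = 0.619; V_true = 0.1849 + 0.5 = 0.685; ratio 0.90. Simulated error is 6.3%.
- Most conservative: BMI, neurology SD 8.1 (n = 100) v normotensive 6.8 (n = 50). Pooled variance = (99×65.61 + 49×46.24)/148 = 59.20; V_pooled = 1.776; V_true = 0.656 + 0.925 = 1.581; ratio 1.12. Simulated error is 3.8%.
- Across all these comparisons the SD ratio (larger group to smaller) is 0.86 to 1.19 and Student's error is 3.8% to 6.3%. Welch's is about 5.0% in each.
- ANOVA at 100/50/50/50: 4.7% to 5.4%, against 5.0% for Welch's ANOVA.

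**4. Equal planned sizes.** With n1 = n2, V_pooled equals V_true. Pulmonary oedema v a control group at 50 v 50 gives 5.0% to 5.1%, even for BMI with SDs 9.2 v 6.8 (ratio 1.35).

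**5. Largest contrast in Table 3.** Birthweight SD is 588 g in HELLP/renal impairment (n = 23) against 906 g in neurology (n = 86). Pooled variance = (22×588² + 85×906²)/107 = 723,154; V_pooled = 723,154×(1/23 + 1/86) = 39,850; V_true = 15,032 + 9,545 = 24,577; ratio 1.62. Simulated error is 1.3%. Against uncomplicated pre-eclampsia (SD 961, n = 54) it is about 1.9%. Both are conservative.

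**6. Range if outcome SDs differed more (assumed), 100 v 50.**

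| SD ratio, larger group to smaller | Student | Welch |
|---|---|---|
| 0.5 | 11.1% | 5.1% |
| 0.67 | 8.6% | 5.0% |
| 0.8 | 6.8% | 5.0% |
| 1.25 | 3.5% | 5.0% |
| 1.5 | 2.6% | 4.9% |
| 2 | 1.7% | 5.0% |

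On the conservative side, for a difference of 0.5 root-mean-square SDs, Student has 80.1% power against Welch's 86.8% at ratio 1.5, and 78.9% against 89.4% at ratio 2.

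**7. Cost of Welch when SDs are equal.** Power falls from 81.9% to 81.7% at 100 v 50 (effect 0.5) and from 79.2% to 79.1% at 25 v 25 (effect 0.8). A repeat run at 100 v 50 gave 81.8% to 81.5%, so the loss is about 0.1 to 0.3 points.

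**The case against.** The strongest reply is that this is a condensed biobank article offering a general menu of tests. No primary outcome is attached, each derived study needs its own ethics approval, and which variance version to use is ordinary analysis-plan detail. The t-test is also conditional: variables whose spread differs because of skew would often go to Mann–Whitney or Kruskal–Wallis. These points lower the weight of the matter. They do not remove it, because the article is not silent: it names the pooled tests for a design that is 2:1 in its largest group.

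A reader might also infer three stronger things that the document does not support.

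- That stated error rates or power are wrong. None are stated, and the worked examples are 25 v 25, where unequal SDs hardly matter.
- That the groups' SDs are already shown to differ. Table 3 covers background and delivery variables only, with no biomarker, Doppler or cardiac measure. Among the four groups with planned sizes the SDs are compatible with equality (Bartlett p 0.27 to 0.94). The birthweight contrast comes from HELLP/renal impairment, which has no planned size. Its pairwise F tests give p = 0.014 to 0.024 without adjustment for multiplicity, but the five-group Bartlett test gives p = 0.13.
- That false positives run at 8% to 11%. That needs the smaller group to have 1.5 to 2 times the SD, which nothing in the document shows; the two birthweight contrasts above err in the conservative direction.

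**Conclusion.** The point holds as a minor one. Equal-variance tests are named, spread plays no part in choosing a test, and eclampsia comparisons are planned at 100 v 50. On the document's own SDs for groups with planned sizes, Student's error is about one percentage point either side of an assumed two-sided 5%, and ANOVA's is closer still. For birthweight at the enrolled HELLP/renal sizes it drops to about 1.3% to 1.9%. Larger departures, in either direction, depend on outcome SD ratios of 1.5 to 2 that are assumed.

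The planned 50 v 50 comparisons and the 25 v 25 examples are essentially unaffected. All error rates here assume normal data and take the SDs in Table 3 as the true ones.

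**What to change.** In section 3.5, replace Student's t-test with Welch's t-test and one-way ANOVA with Welch's ANOVA, and report the matching unequal-variance confidence intervals. The rank-test alternatives can stay as they are. The change is one of wording, and both tests are available in SPSS and R, the software already named. If variances are truly equal, the price is about 0.1 to 0.3 points of power at 25 v 25 or 100 v 50, and somewhat more where sizes are very uneven. Nothing is asked of the regression analyses, because the article specifies no linear model against which a change could be judged.

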#### Power Calculations

Tygerberg University hospital has approximately 8000 high-risk deliveries yearly. Pre-eclampsia affects a large proportion of these deliveries but the exact numbers are not known.

Prospective power calculations for some investigations will not be possible since no reference values or results exist. In addition, the biobank is designed to be open for future research on pre-eclampsia where the research question to date might not be known. Some examples of power calculations for planned analyses are given below.

Cerebral blood flow regulation: To detect a difference in dynamic cerebral autoregulation index of 1, 2 with a standard deviation (SD) of 1.5, 25 women are required in each group [19]. Cerebral biomarkers: To detect a difference of 4 pg/mL between cases and controls for NfL with an SD of 5, 25 women are required per group [20].

In order to extend the comparisons to correlations and sub-analyses, the initial sample size for PROVE was set to 100 women with eclampsia, 50 women with pulmonary oedema, and 50 women in each control group before the first round of analyses are initiated.

### 3.6. Patient and Public Involvement

No input from patients has been solicited in the creation of the database and biobank.

### 3.7. Ethics and Dissemination

Due to the frequency, morbidity, and mortality associated with pre-eclampsia, there is a great scientific and social value to undergird this research. Blanket and broad consent have been avoided, and only research linked to the topic of pre-eclampsia will be conducted. The risk of adverse events is very low. Peripheral blood collection is carried out by an experienced midwife/doctor at the time of routine blood collection. Cerebrospinal fluid is collected from a discarded sample from the anaesthetist during the administration of spinal anaesthesia. MRI imaging in selected participants with eclampsia or cerebral signs has fewer side effects than conventional imaging. Performing transcranial Doppler measurements holds no risks. Participant information databases will be routinely backed up to prevent loss due to technical issues, and samples within the biobank will be secured via routine laboratory safety nets (e.g., the availability of backup freezer space, documentation of usage, etc.).

Blood samples are collected at the same time as routine blood testing, and thus, no additional discomfort is inflicted. Other samples are collected from tissue and fluid that are usually discarded.

No publications will come directly from the biobank. The biobank will provide a source of material for further studies that will each need individual ethics approval.

